## **6.4 Study procedures – detailed overview.**

### **6.4.1 Day 1 – hospital admission.**

At the baseline visit (hospital admission, day 1), subjects will be deemed eligible to take part in the study after the clinical diagnosis of Community Acquired Pneumonia has been made. The following procedures will be completed:

1. Verify inclusion/exclusion criteria
2. Obtain written informed consent
3. Record medical history
4. Collection of demographic information, concurrent disease, concomitant medication use and previous antibiotic therapy.

5. Physical examination (including but not limited to: mild/moderate/severe illness, sputum characteristics, cough, dyspnoea, pleuritic chest pain, chills or rigors and lung sounds) and vital signs (blood pressure, heart rate, temperature, respiration rate and oxygen saturation) will be recorded.
6. The CURB-65 score will be determined. (**C**onfusion, **U**rea > 7 mmol/l, **R**espiratory rate ≥30/min, diastolic **B**lood pressure ≤ 60 en age ≥ **65** years)
7. Blood and urine sample for routine laboratory testing and inflammation study will be obtained.
8. Chest X-rays will be made, if possible both PA and lateral views will be obtained. An AP chest X-ray will be considered acceptable if the patient is unable to stand.
9. Blood cultures will be obtained for all. All blood cultures will be assessed by the laboratory of medical microbiology. All isolates will be tested for susceptibility.
10. If possible an adequate sputum sample will be collected for conventional microbiologic assessment as well as PCR assays and delivered expeditiously to the laboratory to ensure a viable specimen. Freshly expectorated purulent sputum samples must be examined macroscopically for consistency and colour and microscopically to determine the suitability for culture. The presence of > 25 polymorphonuclear leucocytes and < 10 squamous epithelial cells per low power field of a Gram stained specimen is defined as "representative" sputum. Only "representative" sputum specimens as determined by Gram stain should be cultured. If medically indicated, the investigator may attempt to obtain other lower respiratory secretions such as bronchial washing and Broncho Alveolar Lavage (BAL) obtained by bronchoscopy. The specimens will be handled in the same way as sputum specimens.
11. Urine will be collected for detection of *S. pneumoniae* urinary antigen and for *Legionella pneumophila* (subtype 1) urinary antigen.
12. A nasopharyngeal swab will be taken and will be stored for possible future research.
13. Extra blood sample(s) will be taken to assess genetic polymorphisms of corticosteroid-receptors and several other biomarkers.
14. If pleural fluid is present on the Chest X-ray and deemed clinically relevant, a thoracentesis will be performed. Pleural fluid will be handled in the same way as sputum specimens.
15. Patients will be randomised into 1 of three possible treatment strategies.
16. Treatment according to current guidelines will be administered.

#### **6.4.2 Days 2 and 3**

1. Vital signs (pulse, respiration rate, heart rate, blood pressure, and body temperature, Oxygen Saturation) will be recorded three times a day. Each day time to clinical stability will be assessed.
2. Laboratory examination: on indication.
3. Clinical improvement/failure is scored according to Chow et al (appendix B). If treatment needs to be changed because the subjects fails to improve clinically then the subject should be evaluated as a treatment failure and appropriate therapy instituted. This therapy should be recorded.
4. If possible patients will be switched from iv therapy to oral therapy. It is appropriate to switch to oral medication in the following situations: 
  - a. Hemodynamically stable
  - b. If respiratory symptoms such as cough, fever, shortness of breath, and chest pain are improving.
  - c. Oral intake and gastrointestinal absorption adequate.

#### **6.4.3 Days 4-7**

1. Vital signs (pulse, respiration rate, heart rate, blood pressure, and body temperature, Oxygen Saturation) will be recorded three times a day if the patient is still admitted to hospital.

2. Laboratory examination: CRP, PCT, WBC and on indication other tests will be performed until the patient is discharged.
3. Clinical improvement/failure is scored according to Chow et al (appendix B). If treatment needs to be changed because the subjects fails to improve clinically then the subject should be evaluated as a treatment failure and appropriate therapy instituted. This therapy should be recorded.
4. If possible patients will be switched from iv therapy to oral therapy. It is appropriate to switch to oral medication in the following situations:
  - a. Oral temperature or equivalent <37.8 °C (100.3 °F) for at least 24 hours.
  - b. If respiratory symptoms such as cough, shortness of breath, and chest pain are improving.
  - c. Oral intake and gastrointestinal absorption adequate.
  - d. White blood cell count normalizing.
5. Patients may be discharged from the hospital if they meet the following criteria:
  - a. No longer require iv medication, criteria for switching from iv to oral medication mentioned above.
  - b. If their clinical and social situation is stable.
    - i. Clinical stability is defined as:
      1. Temperature <37.8 °C (100.3 °F)
      2. Heart rate <100 beats/min
      3. Respiratory rate < 24 breaths/minute
      4. Systolic blood pressure > 90 mm Hg
      5. Arterial oxygen saturation >90% or pO2 >60 mm Hg on room air
      6. Ability to maintain oral intake
      7. Normal mental status
6. Treatment may be discontinued in the CRP group if the patient shows clinical improvement and the CRP is below 100 mg/L **and** shows a reduction to 50% of the initial value.
7. Treatment may be discontinued in the PCT group if the patient shows clinical improvement and the PCT level is below 0.25 mcg/L **or** shows a reduction to 10% of the initial value.

#### **6.4.5 Day 30 (outpatient visit)**

1. Signs and symptoms identified during the previous days should be assessed. In addition, any new signs and symptoms should be reported.
2. If applicable a sputum sample will be obtained.
3. A chest X-ray will be performed to evaluate radiological response.
4. A pulmonary function test with diffusion capacity will be performed.
5. Investigator evaluation of clinical response will be recorded.
6. On indication laboratory examination may be performed.

### **6.5 Study evaluations**

#### **6.5.1 Definitions of clinical response**

The overall clinical response will be determined by the investigator on day 30. Clinical response will be classified by the investigator as cure, failure, or indeterminate at day 30 as defined in Appendix B. When the investigator is unsure on how to score selected cases, he will consult a colleague to try and reach a consensus. Clinical evaluation of response will be based on the global assessment of the clinical presentation of the subject and compared to the baseline assessment. Clinical assessment will be based upon resolution or improvement of radiological and clinical signs of infection such as resolution of fever, disappearance or diminution in purulent sputum production, and improvement or resolution of dyspnoea, cough and leucocytosis, as well as improvement in general physical condition.

#### **6.5.2 Bacteriological evaluation**

Routine culture techniques and susceptibility testing of isolates should be conducted in the laboratory as appropriate. The results of antigen testing will be interpreted according to the manufacturer's information.

#### **6.5.3 Radiological evaluation**

Consecutive chest X-rays will be evaluated and their evolution will be graded as:

Resolution: disappearance of all radiological signs of infection.

Improvement: significant improvement in the radiological signs of infection compared to baseline.

Failure: no change or worsening in the radiological signs of infection compared to baseline.

#### **6.5.4 Laboratory evaluation**

All clinically significant abnormal laboratory tests occurring during the study will be repeated at appropriate intervals until they either return to baseline or to a level deemed acceptable by the investigator/treating physician.

#### **6.6 Withdrawal of individual subjects**

Subjects can leave the study at any time for any reason if they wish to do so without any consequences. The investigator or treating physician can decide to withdraw a subject from the study for urgent medical reasons. If possible the researcher will document the reason for withdrawal.

#### **6.7 Follow-up of subjects withdrawn from treatment**

Where possible all patients that cease to participate in the study will be followed up according to the schedule of the study protocol. If they refuse, they will return to their own treating physician.

### **7. Safety reporting and monitoring**

#### **7.1 Section 10 WMO event**

In accordance to section 10, subsection 1, of the WMO, the investigator will inform the subjects and the reviewing accredited METC if anything occurs, on the basis of which it appears that the disadvantages of participation may be significantly greater than was foreseen in the research proposal. The study will be suspended pending further review by the accredited METC, except insofar as suspension would jeopardise the subjects' health. The investigator will take care that all subjects are kept informed.

#### **7.2 Adverse events**

Events involving adverse drug reactions, illnesses with onset during the study, or exacerbations of pre-existing illnesses should be recorded. Exacerbation of pre-existing illness, including the disease under study, is defined as a manifestation (sign or symptom) of the illness that indicates a significant increase in the severity of the illness as compared to the severity noted at the start of the trial. It may include worsening or increase in severity of signs or symptoms of the illness, an increase in frequency of signs and symptoms of an intermittent illness, or the appearance of a new manifestation/complication. Exacerbation of a pre-existing illness should be considered when a patient/subject requires new or additional concomitant drug or non-drug therapy for the treatment of that illness during the trial. Lack of or insufficient clinical response, benefit, efficacy, therapeutic effect, or pharmacological action, should not be recorded as an adverse event. The investigator must make the distinction between exacerbation of pre-existing illness due to a complication or manifestation unrelated to the causative agent being treated and lack of therapeutic efficacy. All adverse events will be reported every 6 months by the investigator through the webportal "ToetsingOnline."

### **7.3 Serious adverse events**

A serious adverse event is any untoward medical occurrence or effect that at any dose:

- Results in death
- Is life threatening at the time of the event
- Requires hospitalisation or prolongation of existing inpatients' hospitalisation
- Results in persistent or significant disability or incapacity

Any serious adverse event will be reported to the sponsor as soon as possible. This will be done by phone or email. In all centres the responsibility for reporting lies with the investigator coordinating the trial in the respective centre.

The sponsor will report the SAEs through the webportal "ToetsingOnline" to the accredited METC that approved the protocol, within 24 hours after the sponsor has first knowledge of the serious adverse event.

### **7.4 Follow-up of adverse events**

All AEs will be followed until they have ablated, or until a stable situation has been reached.

Depending on the event, follow up may require additional tests or medical procedures as indicated, and/or referral to the general physician or a medical specialist. SAEs need to be reported till end of study within the Netherlands, as defined in the protocol.

### **7.5 Data Safety Monitoring Board**

The DSMB consists of 3 members who are independent of the set-up and execution of the trial. At least one DSMB member will be an independent statistician. Another member with knowledge about the disease should be represented. The third member should have knowledge about safety effects and ethical dilemmas. The statistician is also the chairman of the board. All members of the DSMB receive the definite protocol of the present study and all revisions. The statistician of the DSMB will convene every six to twelve months and review the results, i.e. results split by experimental and control arms. Only if necessary, the other members of the board will be informed about the interim results. However, the DSMB has the power to recommend termination of the study based on the evaluation of these results. There are typically three reasons a DSMB might recommend termination of the study: safety concerns, outstanding benefit, and futility. The primary mandate of the DSMB is to protect patient safety. If adverse events of a particularly serious type are more common in the experimental arm compared to the control arm, then the DSMB would have to strongly consider termination of the study. This evaluation has to be made in consideration of risk/benefit. In many cases, the experimental arm could cause serious adverse events, but the resulting improvement in survival could outweigh these adverse events.

At the conclusion of a DSMB meeting, the DSMB should inform the findings or conclusions to the study investigators by mail or e-mail. If there is any dispute between the DSMB and study investigators, the DSMB should notify the METC Noord Holland.

The DSMB consists of the following members:

[name], biostatistician.

[name], cardiologist.

[name], ethicist.

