## **3. Study design**

This study will be set up as a Randomised Controlled Trial with a parallel design, patients will be randomly allocated to one of 3 treatment groups. No blinding will be performed, since treating physicians will have to make a decision to continue or withhold treatment based on laboratory evaluations. In order to make the right decision they will have to know whether or not the patient is receiving antibiotics.

Patients will be included at hospital admission and the follow up period is 1 month. The control group will consist of patients getting treated according to common clinical practice.

Patients will be admitted to hospital and receive therapy according to the study protocol. They will be discharged from the hospital when their medical condition and social situation is stable. If patients are discharged and still using antibiotics, blood tests will be performed daily in the participating centre and the researcher will contact the patients by phone to inform them whether or not antibiotic treatment can be discontinued. After discharge the patient will be evaluated at an outpatient visit on day 30. In case of any event an interim visit will be scheduled. If for some reason a patient fails to perform an outpatient blood test, antibiotics will be continued until the next blood test or for a total of 7 days and the reason for failure will be documented.

This study will be conducted in the Medical Centre Alkmaar, the Isala clinics in Zwolle and the Slotervaart hospital in Amsterdam.

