### **9.2 Recruitment and consent**

Patients or their legal representatives will be asked to participate in this study by the attending physician or the investigator at the time of hospital admission. All patients will receive the patient information letter and informed consent form. They will be given one hour to consider their decision. Prior to consent blood tests may be performed and antibiotics can be started, since this is all part of regular care and in the patients interest.

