### ***10.2 Monitoring and quality assurance***

The conduct of the study and data entries will be monitored by an internal monitor. This will be done by [name] who will select a sample of cases and check them for irregularities. If any are found, the monitor may choose to select a larger sample or review all available data. He will report the irregularities to the sponsor who is responsible for correcting any mistakes.

All adverse events will be analysed periodically by the statistician of the DSMB. If adverse events of a particularly serious type are more common in the experimental arm compared to the control arm he will inform the sponsor and other members of the DSMB which may then take actions as described in chapter 7.5.

All serious adverse events will be reported to the accredited METC.

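### DSMB communication (7.5, 10.2): the wording does not stop by-arm interim results reaching the investigators, and it sends a serious-event imbalance to the sponsor at the same time as the rest of the board

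*Protocol*

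**What the plan says.** **Review.** Section 7.5 has the DSMB statistician "review the results, i.e. results split by experimental and control arms" every six to twelve months. The other two members learn of interim results only where this is needed. The listed grounds for recommending termination are safety, outstanding benefit and futility.

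**Reporting out of the board.** The same section continues: "At the conclusion of a DSMB meeting, the DSMB should inform the findings or conclusions to the study investigators by mail or e-mail".

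**Serious-event imbalance.** Section 10.2 has the statistician analyse adverse events periodically. The trigger is: "If adverse events of a particularly serious type are more common in the experimental arm compared to the control arm". In that case "he will inform the sponsor and other members of the DSMB which may then take actions as described in chapter 7.5".

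**Openness of the trial.** Section 3: "No blinding will be performed, since treating physicians will have to make a decision to continue or withhold treatment based on laboratory evaluations".

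**Roles.** Under section 9.2 patients "will be asked to participate in this study by the attending physician or the investigator at the time of hospital admission". Section 6.5.1: "Clinical response will be classified by the investigator as cure, failure, or indeterminate at day 30". That rating is a global assessment against baseline.

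**The concern.** In an open-label trial the staff know each patient's arm. The pooled comparison between arms, across all three centres, can still be protected, and keeping it inside an independent board is a main reason for having one.

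If that comparison reaches people who enrol, treat or rate patients, a chance trend early in the trial can change who is approached, how readily antibiotics are continued or stopped, and how a borderline day-30 case is classed. The primary endpoint (duration of antibiotic treatment) and one secondary endpoint (clinical response) contain enough judgement to be affected. Mortality is much less exposed.

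The concern with section 10.2 is related but separate: the sponsor could act on one statistician's signal before the clinical and ethical members have weighed it.

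**Working it through.** The protocol gives no figure on this point, so the check sets the relevant sections side by side.

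**1. What may leave the board.** Section 7.5 uses two terms. Interim results are restricted even within the board. Findings or conclusions go to the study investigators after a meeting. The second term is undefined, and no sentence confines it to a recommendation or bars by-arm content. Disclosure is therefore allowed but not prescribed. The limit on the other board members is written down; a corresponding limit on what investigators may receive is not.

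**2. Who receives what.** The two routes differ:

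| | Section 7.5 | Section 10.2 |
|---|---|---|
| Sender | DSMB, after a meeting | DSMB statistician |
| Content | Findings or conclusions, undefined | Particularly serious event types more common in the experimental arm |
| Direction | Either (harm, benefit, futility) | Harm in the experimental arm only |
| Recipient | Study investigators | Sponsor, together with the other board members |

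Section 10.2 does not name the investigators. Sections 10.4 and 10.5 do write sponsor and investigator as a joint party, so the two roles may not be far apart, but the protocol does not say that they coincide.

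**3. Order of events in 10.2.** The board acts after the statistician's notice, and the sponsor gets that notice too. The sponsor therefore knows of the imbalance before the board has assessed it.

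**4. What the recipients can influence.**
- *Enrolment:* the attending physician or the investigator approaches patients (9.2).
- *Duration, control arm:* the treating physician may lengthen treatment (5.2).
- *Duration, guided arms:* sections 5.3 and 5.4 give numeric marker thresholds. Section 6.4.3 makes stopping permissive and adds clinical improvement, without saying who judges it. (The two statements need reconciling in their own right.) Appendix A lets the treating physician's safety judgement override a stop. After discharge the researcher phones the patient about stopping (section 3).
- *Withdrawal:* the investigator or the treating physician may withdraw a subject for urgent medical reasons (6.6).
- *Day-30 response:* rated by the investigator (6.5.1, 8.4.4).
- *Analysis:* by the investigator with an independent check (8.5), although 8.4.1 assigns it to an independent statistician.

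The investigator's influence is clear for response, shared for enrolment, and partial for duration, where most decisions lie with treating physicians.

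**5. Size.** A bias estimate would need the content of the messages, the accrual rate and the effect of disclosure on behaviour. The protocol gives none of these. It gives a review interval in months but no accrual rate, so even the number of patients enrolled after the first review cannot be derived.

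**The case against.** **The paragraph can be read innocently.** Section 7.5 withholds interim results from two of its own three members unless needed. It would be odd for it also to intend mailing by-arm results to investigators. On this reading they receive only the outcome of the meeting. This stands as far as it goes: the text does not require disclosure. It does not exclude it either, and an undefined term is a weak safeguard.

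**Much is already open.** Allocation is known, each serious event goes to the sponsor as soon as possible (7.3), and adverse events are reported six-monthly (7.2). The sponsor could tally serious events by arm unaided. This stands for the sponsor and reduces what the 10.2 change can achieve. It has less force for 7.5: single-event reports do not routinely give each investigator the pooled comparison across three centres.

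**Prompt notice serves safety.** Section 7.1 obliges the investigator to inform subjects and the ethics committee if participation proves more disadvantageous than foreseen. Delaying news of a serious imbalance could work against that. This stands as a condition: the 10.2 change is acceptable only if board review is prompt and the duties in 7.1 and 7.3 are untouched.

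**A DSMB charter may settle this.** Possibly, but the protocol itself states the rule, and that wording should be sound.

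**Stronger readings to avoid.** A reader might infer that every adverse-event imbalance is passed on, that investigators are told of it under 10.2, or that one group recruits, treats and rates. The text supports none of these. The 10.2 trigger is narrow and one-directional, its outside recipient is the sponsor, and treatment decisions lie mainly with treating physicians.

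**Conclusion.** The concern holds as a weakness in a stated communication rule. Section 7.5 leaves room for by-arm interim results to reach investigators who may recruit and who rate day-30 response. Section 10.2 gives the sponsor a serious-event signal before the full board has considered it. The 7.5 part is the stronger of the two. The 10.2 part is mainly about letting the board judge first.

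The conclusion assumes that the wording will be applied as written and that no separate charter narrows it. It does not say that by-arm results will be disclosed or that any bias will follow. The likely size is unknown and cannot be calculated from the protocol. The change is worth making because it costs almost nothing and protects information that open allocation does not already give to each investigator.

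**What to change.** **Section 7.5.** Replace the reference to findings or conclusions with the DSMB's recommendation only: continue, modify, pause or stop. State that by-arm data stay within the DSMB unless a recommended change cannot be acted on without them.

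**Section 10.2.** Have the statistician take an imbalance of the kind described there promptly to the full DSMB. The DSMB, rather than the statistician alone, then informs the sponsor and the ethics committee. Add that the section 7.1 duty and individual SAE reporting under 7.3 are unchanged.

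**Cost.** Two sentences in the protocol, repeated in a DSMB charter if there is one. No effect on sample size, visits or clinical rules. The one downside is that the sponsor may hear of a signal slightly later than under the present text, which is why the step to the full board has to be prompt.
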